### Surgery

Patients will undergo resection of their rectal cancer at a time recommended by their surgeon (generally 7–10 weeks after completion of pCRT). Patients with an excellent clinical and radiological response may be observed under a “watchful waiting” programme if agreed with their surgeon.

Surgery may include open, laparoscopic, robotic or transanal total mesorectal excision approach. This will include both restorative low anterior resection, or abdomino-perineal resection with permanent end-colostomy.

### Post-operative management

Treatment after discontinuation of trial treatment is at the discretion of the patient’s clinician. Adjuvant chemotherapy may be administered on the recommendation of the treating clinician and its use will be recorded.

Blood tests will be performed on the first day of pCRT, prior to starting chemotherapy, to assess the impact of trial medication on the mGPS and NLR. Clinical assessments including IBDQ-B questionnaire will be conducted on Trial Weeks 3, 5 and 7 [62].

Week 13 assessments will be performed 6 weeks (+/− 7 days) after completion of pCRT and prior to surgery. An MRI scan for mrTRG must be completed 6–8 weeks after completion of pCRT and must be prior to surgery. The postoperative visit will include assessment of length of hospital stay after surgery and any readmission data. Subsequent follow-up is annually.

### Data to be collected

The study will collect data on: baseline patient and tumour status; treatment delivery; baseline and post-pCRT MRI assessments; clinical and laboratory toxicity assessments; baseline and resection histopathology; followup data for PFS and OS (Table 1).

**Table 1 Tab1:** Schedule of Assessments

Treatment Period – Trial Week											
	Baseline / screening	1	2	3	4	5	6	7	13	4–6 weeks post-op	Follow up
Informed consent	X										
History	X									X	
Physical exam ^b^	X			X		X		X		X	
Trial medication start		X									
Preoperative CRT			X	X	X	X	X	X			
Concomitant meds	X			X		X		X	X		X
Trial med compliance				X		X		X	X		
Adverse events				X		X		X	X		X
Haematology	X		X	X	X	X	X	X	X		
Chemistry incl. CRP	X		X	X	X	X	X	X	X		
CEA	X										X
Serum pregnancy test	X										
Resected rectal tissue										X	
CT scan	X										X
Pelvic MRI	X								X ^o^		
Lower GI endoscopy	X										X

### Statistical methodology

#### Sample size

The primary endpoint of this trial is rates of favourable mrTRG (grades 1 or 2). This will be analysed using ordinal regression with 4 ordered categories of mrTRG (1, 2, 3 and 4–5) to provide greater sensitivity. Based on published data using MRI 6–8 weeks after pCRT, the expected rate of mrTRG in the control group is 9% grade 1, 39% grade 2, 20% grade 3 and 32% grades 4–5. A 35% relative increase in favourable mrTRG would be a worthwhile difference to inform a phase III trial.

Based on an ordinal proportional odds assumption, a sample size of 222 patients (111 treated with SIM and 111 controls) will have > 80% power to detect a change in mrTRG rates to 17% grade 1, 48% grade 2, 16% grade 3 and 19% grades 4–5 with 95% confidence.

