**Methods:**

A double-blind phase 2 trial will randomise 222 patients planned to receive long-course fluoropyrimidine-based pCRT for rectal adenocarcinoma at 18+ sites in New Zealand and Australia. Patients will receive simvastatin 40 mg or placebo daily for 90 days starting 1 week prior to standard pCRT. Pelvic MRI 6 weeks after pCRT will assess mrTRG grading prior to surgery. The primary objective is rates of favourable (grades 1–2) mrTRG following pCRT with simvastatin compared to placebo, considering mrTRG in 4 ordered categories (1, 2, 3, 4–5). Secondary objectives include comparison of: rates of favourable pathTRG in resected tumours; incidence of toxicity; compliance with intended pCRT and trial medication; proportion of patients undergoing surgical resection; cancer outcomes and pathological scores for radiation colitis. Tertiary objectives include: association between mrTRG and pathTRG grouping; inter-observer agreement on mrTRG scoring and pathTRG scoring; studies of T-cell infiltrates in diagnostic biopsies and irradiated resected normal and malignant tissue; and the effect of simvastatin on markers of systemic inflammation (modified Glasgow prognostic score and the neutrophil-lymphocyte ratio). Trial recruitment commenced April 2018.

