### Rationale for trial endpoints

#### mrTRG and pathTRG

MRI-based tumour regression grading (mrTRG), a 5-point system validated by the MERCURY group [35], is used for the primary endpoint in this trial as it permits much more sensitive and reliable preoperative assessment of tumour regression following pCRT in rectal cancer patients than other methods used currently (endoscopy, CT, PET-CT, endoluminal ultrasound or routine MRI) [36, 37]. mrTRG has proven to be a good predictor of pathological tumour regression grading (pathTRG) after pCRT [38], as well as independently predicting DFS and OS [39]. In a separate study, mrTRG identified ten times as many pathological CR patients as clinical inspection of the tumour following pCRT, with no compromise of the false-positive rate [37].

The rate of favourable (grades 1–2) mrTRG is the primary endpoint for the SPAR trial, based on three recently-published pCRT rectal cancer trials [40, 41]. In the MERCURY-II trial [40] favourable (grades 1–2), intermediate (grade 3) and unfavourable mrTRG (grades 4–5) had 3-year DFS of 82, 72 and 61% respectively ([name], personal communication). The phase 2 EXPERT and EXPERT-C trials evaluated neoadjuvant chemotherapy followed by pCRT [41]. On pooled analysis of these trials, mrTRG performed 4 weeks after completion of pCRT was evaluable in 85.5% of 269 patients; favourable (mrTRG 1–2), intermediate (mrTRG 3) and unfavourable (mrTRG 4–5) outcomes were seen in 41.7, 30.9 and 27.4%, respectively. pathTRG was evaluable in 86.9% of 244 resected patients with favourable, intermediate and unfavourable scores seen in 35.4, 29.7 and 34.9% respectively. Favourable mrTRG was independently associated with PFS (HR 0.37, *p* < 0.001) and OS (HR 0.44, *p* = 0.006) [41].

While the mrTRG training provided in SPAR has been shown to achieve moderate-to-excellent agreement between expert and training radiologists [42], it is important to show independently in the SPAR trial that mrTRG can be successfully and reproducibly performed in multiple centres, and shows a strong correlation with pathTRG and clinically-important cancer outcomes.

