## Methods/design

SPAR is a randomised phase 2 study with the overall aim to evaluate the effect of SIM on efficacy and toxicity of pCRT in rectal cancer patients, and on systemic and local inflammatory responses. Recruitment of 222 patients is required to address the primary objective. The study will recruit patients from participating AGITG hospitals/institutions in Australia and New Zealand.

Primary Objective:

The primary objective is to compare rates of favourable (grades 1–2) mrTRG (by central review) following pCRT with SIM versus with placebo, considering mrTRG in 4 ordered categories: 1, 2, 3, 4–5 (proportion of patients with favourable mrTRG in SIM and placebo groups). mrTRG will be assessed by comparison of the MR scan taken after pCRT with the scan before pCRT, which will be performed using the MERCURY protocol (38), and images analysed as described [38].

Secondary Objectives:

Secondary objectives are to compare between the SIM and placebo groups treated with pCRT: 1) The rate of favourable (grades 1–2) pathTRG in resected tumours by central review (proportion of patients with favourable pathTRG at surgical resection); 2) The incidence of > grade 2 acute GI and non-GI adverse events, assessed using CTCAE version 4.03; 3) The incidence of late GI adverse events; 4) Compliance with intended pCRT (proportion of patients completing > 90% of planned pCRT without dose reductions or delays); 5) Compliance with trial medication (proportion of patients receiving > 90% of the planned trial medication); 6) The proportion of patients undergoing surgical resection post-pCRT; 7) 3-year local recurrence (LR) rate, disease-free survival (DFS) and cancer-specific survival (CSS) (3-year LR rate, DFS and CSS); 8) the pathological scores determined by the central pathologist for radiation colitis in irradiated rectum in the resected specimen (radiation colitis scores).

Translational Science Objectives:

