**Fig. 1 Fig1:**
[figure not shown]
SPAR SPIRIT diagram. Abbreviations: HGD; high grade dysplasia. LC; long course. pCRT; preoperative chemoradiation. FP; fluoropyrimidine. cT/cN; clinical stage. LVI; lymphovascular invasion. ®; randomisation. Gy; gray. fx; fraction. BD; twice daily. 5FU; 5-fluorouracil. mrTRG: magnetic resonance assessed tumour regression grade

Treatment allocation will be balanced using minimisation for the following characteristics:
trial siteAJCC clinical T stage (< 4 vs. 4)AJCC clinical N stage (< 2 vs. 2)the presence of either mesorectal fascia involvement (tumour margin within 1 mm of the fascia) or lymphovascular space invasion (including extramural venous invasion) on MRI

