#### Statistical analysis

Intention-to-treat analysis of results will be the primary analysis. In addition, an exploratory per protocol analysis will also be conducted which will exclude ineligible patients, those not taking trial medication when starting pCRT and those who withdraw their consent to participate prior to response evaluation.

The primary endpoint and all secondary endpoints expressed as proportions will be estimated, together with corresponding 95% confidence intervals based on exact binomial distributions. Kaplan-Meier curves will be calculated for all time-to-event endpoints. Rates at specific points in time (e.g. 3-year local recurrence rate) will be estimated from these Kaplan-Meier curves.

Inter-observer agreement is defined as the degree of agreement in mrTRG (or pathTRG) results when reviewed by the central radiologist (or pathologist) and the reporting site radiologists (or pathologists). Results for each of mrTRG and pathTRG will be reported separately in a 3X3 grid comparing favourable, intermediate, and unfavourable scores between central and site radiologists and pathologists respectively. Inter-observer agreement will be assessed using a weighted kappa statistic > 0.40 is defined as moderate agreement. This will be assessed for mrTRG after recruitment of 35 randomised patients to ensure procedural consistency and again at the conclusion of the trial.

Adverse events in each arm will be tabulated and graded according the NCI CTCAE version 4.03.

For analysis of translational objectives, association between CD3+ and CD8+ T-cell infiltrates in diagnostic rectal cancer biopsies and pathTRG following pCRT will be evaluated using the chi-square test for trend. The effect of SIM on subsets of T-cells in tumours and normal tissue will be evaluated by comparison of distribution of scores for each cell type in SIM and placebo groups using the chi-square test for trend. Changes in the NLR and mGPS over time will be analysed using repeated measures ANOVA.

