#### Interim analyses and early stopping

No formal interim analysis for efficacy is planned but review of safety data by the AGITG Independent Safety and Data Monitoring Committee (ISDMC) is planned. No early stopping for larger-than-expected differences in mrTRG rates is planned because this endpoint is a putative surrogate for improved patient outcome. Demonstrating a significant difference in the clinically-important DFS and OS endpoints requires a much larger phase III trial.

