## Discussion

Little progress has been made in the management of T3 rectal cancer in the last 10 years. The findings in several retrospective studies that statin use in patients undergoing pCRT appears to confer higher pathological regression rates, more pathological CR [22–24] and also lower RT toxicity [16, 22–24], led us to mount this phase II RCT. We chose to start statin therapy 1 week prior to pCRT to observe for clinical and biochemical effects independent of pCRT, and continue it for 3 months to allow maximum interaction with CRT. The use of a standard dose of simvastatin is pragmatic; 40 mg per day is the highest dose that is well tolerated. The evaluations are comprehensive, including comparative treatment-induced changes in MR scans, pathological evaluation of the resected specimen, and blood biochemical changes, as well as longer-term tumour outcomes (PFS and OS). With this sample size of 222 patients (111 simvastatin and 111 placebo), we should be able to observe meaningful differences in these parameters if simvastatin has any beneficial effect in the treatment of this disease.

If this study has a positive result, a larger RCT will be needed to confirm and validate the merit of statins in the preoperative management of rectal cancer, especially long-term clinical outcomes. Such a finding could also lead to studies of statins in conjunction with radiation and chemotherapy in a range of other malignancies, as well as further exploration of possible mechanisms of action and interaction of statins with both radiation and chemotherapy. The translational substudies undertaken with this trial will provisionally explore some of these possible mechanisms, and the tissue and data can be made available for further investigations.

This trial is an important opportunity to identify whether assessment of systemic inflammation (reflected in the neutrophil-lymphocyte ratio and the mGPS) and the local inflammatory response (through characterising infiltrating immune cells) could be important translational research components of a subsequent phase III trial of statins in rectal cancer patients. Additionally, it will allow us to evaluate the impact of SIM on the interaction of specific T-cell infiltrates in pre-pCRT biopsies with pathTRG in the resected tumours, and with normal tissue inflammation after pCRT.

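### The >80% power requires nearly all 222 randomised patients to have a graded mrTRG; no allowance is made for missing or unreadable scans

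*Protocol article*

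**What the plan says.** The Sample size section of the protocol article says that "a sample size of 222 patients (111 treated with SIM and 111 controls) will have > 80% power" to detect a shift in the four ordered mrTRG categories, using ordinal regression under proportional odds at 95% confidence.

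The same number is the enrolment target. The Abstract says "A double-blind phase 2 trial will randomise 222 patients", and Methods/design says "Recruitment of 222 patients is required to address the primary objective". No larger randomised number and no attrition allowance is given anywhere in the article.

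The rationale for the mrTRG and pathTRG endpoints reports, for a pooled analysis of two earlier phase 2 trials, that "mrTRG performed 4 weeks after completion of pCRT was evaluable in 85.5% of 269 patients".

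Two statements concern what the trial can show. The Discussion lists imaging, pathology, biochemistry, PFS and OS, and then says "we should be able to observe meaningful differences in these parameters if simvastatin has any beneficial effect". The section on interim analyses says "Demonstrating a significant difference in the clinically-important DFS and OS endpoints requires a much larger phase III trial".

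**The concern.** A sample size for a graded imaging endpoint normally separates patients randomised from patients with a usable grade. Here one number serves as both. A grade needs a baseline scan, a second scan in its time window and before surgery, and a central reading that compares the two. Any patient lost at one of these steps reduces the information behind the primary comparison, and an analysis plan written later cannot put back patients who were not enrolled.

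The result is meant to inform a decision on phase III. A null result would be read as coming from a trial with more than 80% power, with nothing in the text to say that this depends on nearly complete scans.

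**Working it through.** **Inputs (Sample size section).** Control, grades 1 / 2 / 3 / 4–5: 0.09, 0.39, 0.20, 0.32. Simvastatin: 0.17, 0.48, 0.16, 0.19. Allocation is 1:1. Sidedness is not stated; two-sided 5% is assumed.

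**Odds ratios implied by the percentages.**
- Grade 1 v rest: (0.17/0.83)/(0.09/0.91) = 2.071
- Grades 1–2 v rest: (0.65/0.35)/(0.48/0.52) = 2.012
- Grades 1–3 v rest: (0.81/0.19)/(0.68/0.32) = 2.006

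The mean of the log odds ratios gives 2.029; a rounded planning value is 2.00.

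**Formula (Whitehead, proportional odds).** Power = Φ( ln(OR) × √[N/12 × (1 − Σp̄³)] − 1.96 ), where p̄ is the mean of the two distributions: 0.13, 0.435, 0.18, 0.255. Then Σp̄³ = 0.107 and 1 − Σp̄³ = 0.893.

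**Step 1: reproduce the stated figure.** With N = 222, √(18.5 × 0.893) = 4.065. At OR 2.012, 0.699 × 4.065 − 1.96 = 0.88, so power is 81.1%. At OR 2.00 it is 80.4% and at OR 2.029 it is 82.0%. Simulation from the listed percentages agrees: 81.1% with a rank (score) test and 82.0% with a proportional-odds likelihood-ratio test. The stated >80% is reproduced, with all 222 graded.

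**Step 2: graded patients needed for 80%.** N = 12 × (1.96 + 0.842)² / [ln(OR)² × 0.893].
- OR 2.00: 219.5, so 220 (99% of 222)
- OR 2.012: 215.8, so 216 (97%)
- OR 2.029: 210.5, so 211 (95%)

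The loss that can be absorbed is therefore 2 to 11 patients, and 6 at the favourable-grade odds ratio.

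**Step 3: power by share evaluable**, with ungraded patients dropping out at random.

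| Evaluable | Graded N | OR 2.00 | OR 2.012 | OR 2.029 |
|---|---|---|---|---|
| 100% | 222 | 80.4% | 81.1% | 82.0% |
| 95% | 210.9 | 78.4% | 79.1% | 80.1% |
| 90% | 199.8 | 76.2% | 76.9% | 77.9% |
| 85.5% | 189.8 | 74.1% | 74.8% | 75.8% |

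Simulation with 95 per arm gives 74.9% (rank test) and 75.1% (proportional odds).

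**Step 4: sidedness.** At OR 2.012, a one-sided 5% test would give about 88% with 222 graded. With 190 graded it would give Φ(2.629 − 1.645) = Φ(0.984), about 84%. The two-sided reading is the one that lands just above 80%, so it is the natural one.

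**Step 5: the Discussion sentence.** Even on mrTRG, a smaller benefit is not well covered. At OR 1.5 (48% to 58% favourable), with 1 − Σp̄³ = 0.896 for that pair of distributions and all 222 graded, 0.405 × √(18.5 × 0.896) − 1.96 = −0.31, so power is about 38%.

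**The case against.** The strongest reply is that nothing has been miscalculated: >80% is correct for 222 graded patients. That stands. The point is an unstated condition and a missing margin.

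It is also fair to say that 85.5% is not a planning assumption for SPAR. It comes from trials of neoadjuvant chemotherapy followed by chemoradiation, with MRI at 4 weeks, whereas SPAR scans at 6–8 weeks. SPAR also requires measurable disease on baseline MRI and a second scan before surgery, and it trains its radiologists. Evaluability may well be higher. That too stands, so 75% is a scenario. It does not remove the point, since power at OR 2.012 falls below 80% once about 3% of scans are lost.

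The threshold is soft, because the inputs are whole percentages. On the largest of the three cumulative odds ratios (2.071), 199 graded patients suffice and about 10% could be lost. That is the most generous reading, and it still gives only 78% at 85.5% evaluable. At 95% evaluable the shortfall at OR 2.012 is under one percentage point.

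Three stronger readings are tempting, and the article does not support them.
- A reader might infer that withdrawals are expected, from the reference to "those who withdraw their consent to participate prior to response evaluation". That phrase only defines an exclusion from an exploratory per-protocol set and gives no rate.
- A reader might count ungraded patients as grades 4–5 under intention to treat and derive a much larger loss of power. The article contains no such rule, and handling of missing grades may be set in the full protocol or analysis plan.
- A reader might take the Discussion as claiming power for PFS and OS. It attaches no power figure to them, and its next paragraph asks for a larger trial, especially for long-term outcomes. The conflict with the section on interim analyses is real, but it is one of loose wording.

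**Conclusion.** The stated power holds only if essentially all 222 randomised patients have a centrally graded mrTRG, and the design includes no allowance for any who do not. On the common odds ratio readings from 2.00 to 2.029, 80% power needs 211–220 graded patients (95–99%), with 216 (97%) as the central value. Power is about 77% at 90% evaluable and about 75% in the 85.5% scenario, a loss of roughly 4 and 6 percentage points from the central 81.1%.

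This rests on a two-sided 5% test, the stated distributions, and ungraded patients being missing at random. The article does not show that SPAR's actual power is 75%; it shows that >80% is conditional and that the condition is not stated. The wording conflict in the Discussion is secondary.

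**What to change.** 1. **Sample size section.** State the condition, for example: *222 patients will be randomised; power above 80% (two-sided 5%) assumes that at least about 97% have an evaluable mrTRG; power is about 77% at 90% evaluable and about 75% at 85.5%.* This is a text change with no added patients. The cost is a slightly less favourable stated figure. Restoring 80% by numbers at 85.5% evaluable would mean randomising about 253 (216/0.855 = 252.6). That is not proposed here, because 85.5% is not established for SPAR.

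2. **Discussion.** Limit the sentence on what 222 patients can show to the mrTRG effect the trial is powered for, and describe PFS and OS as not powered, in line with the section on interim analyses. The cost is one sentence.

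3. **Optional.** The Design section says "Treatment allocation will be balanced using minimisation for the following characteristics". The patient-level factors among them (T stage, N stage, and mesorectal fascia or lymphovascular involvement) could be covariates in the proportional-odds model, if the analysis plan does not already provide for this. They are recorded anyway. Any gain in power depends on how prognostic they are, which the article does not give, so no specific recovery should be claimed.

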#### Statistical analysis

Intention-to-treat analysis of results will be the primary analysis. In addition, an exploratory per protocol analysis will also be conducted which will exclude ineligible patients, those not taking trial medication when starting pCRT and those who withdraw their consent to participate prior to response evaluation.

The primary endpoint and all secondary endpoints expressed as proportions will be estimated, together with corresponding 95% confidence intervals based on exact binomial distributions. Kaplan-Meier curves will be calculated for all time-to-event endpoints. Rates at specific points in time (e.g. 3-year local recurrence rate) will be estimated from these Kaplan-Meier curves.

Inter-observer agreement is defined as the degree of agreement in mrTRG (or pathTRG) results when reviewed by the central radiologist (or pathologist) and the reporting site radiologists (or pathologists). Results for each of mrTRG and pathTRG will be reported separately in a 3X3 grid comparing favourable, intermediate, and unfavourable scores between central and site radiologists and pathologists respectively. Inter-observer agreement will be assessed using a weighted kappa statistic > 0.40 is defined as moderate agreement. This will be assessed for mrTRG after recruitment of 35 randomised patients to ensure procedural consistency and again at the conclusion of the trial.

Adverse events in each arm will be tabulated and graded according the NCI CTCAE version 4.03.

For analysis of translational objectives, association between CD3+ and CD8+ T-cell infiltrates in diagnostic rectal cancer biopsies and pathTRG following pCRT will be evaluated using the chi-square test for trend. The effect of SIM on subsets of T-cells in tumours and normal tissue will be evaluated by comparison of distribution of scores for each cell type in SIM and placebo groups using the chi-square test for trend. Changes in the NLR and mGPS over time will be analysed using repeated measures ANOVA.

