## Background

### Summary of clinical condition and current treatments

Colorectal cancer (CRC) is common: 3016 cases were diagnosed in New Zealand (NZ) in 2012 with 1283 deaths [1] and rectal cancer represents about one-third of all colorectal cancers in NZ [2]. In Australia, 5114 rectal cancer cases were diagnosed in 2011 with 2018 deaths in 2012 [3]. Rectal cancer usually presents with locally-advanced T3 disease that requires ‘short course’ radiotherapy (SCRT) or, more commonly, ‘long course’ preoperative chemoradiation (pCRT – in which either infusional 5-fluorouracil (5FU) or oral capecitabine are administered concurrently with radiotherapy) for 5–6 weeks before surgery, and often adjuvant post-operative chemotherapy. While these advances in the management of resectable rectal cancer have reduced local relapse to < 10% in most patients, those with higher tumour stage, or evidence on staging MRI scan of invasion of local nodes, mesorectal fascia or blood vessels, have substantially higher local relapse rates and poorer overall survival (OS) [4]. In addition, distant relapse still occurs in 25–30% of patients, with most dying within 5 years [5]. Adding more drugs (such as oxaliplatin or irinotecan) to pCRT increases toxicities but with no improvement in cancer outcomes [6]. Other strategies are being explored in phase 2 and 3 trials but none have yet changed the standard of pCRT (or, less commonly, SCRT).

Unfortunately, the majority of patients (about 60%) with high-risk tumours have poor responses of their tumour to pCRT, and this group have double the risk of relapse compared to good responders [7]. Furthermore about 10% of surviving patients suffer from long-term significant bowel toxicity from RT. [5, 8] There is a clear need for improved efficacy and reduced toxicity in the large number of rectal cancer patients treated with pCRT every year in NZ and Australia.

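### The 3-year local recurrence rate is to be read from Kaplan-Meier curves although death without local recurrence competes with it; the effect is small, and cumulative incidence is the better estimator.

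*Protocol article*

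**What the plan says.** Objective 7 of the secondary objectives (Methods/design) compares the arms on "3-year local recurrence (LR) rate, disease-free survival (DFS) and cancer-specific survival (CSS"), with 3 years as the time point.

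The Statistical analysis section assigns one estimator to every such endpoint: "Kaplan-Meier curves will be calculated for all time-to-event endpoints". It then takes LR as its example: "Rates at specific points in time (e.g. 3-year local recurrence rate) will be estimated from these Kaplan-Meier curves". It names no competing-risk method, and it does not say how a death without LR enters the LR curve.

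The background (Summary of clinical condition and current treatments) says that current management advances "have reduced local relapse to < 10% in most patients". It also puts distant relapse at 25 to 30% of patients, most of whom die within five years.

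The endpoint labels differ elsewhere. Data to be collected lists "followup data for PFS and OS", and the Discussion again gives PFS and OS as the longer-term outcomes. Neither is among the secondary objectives.

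**The concern.** Kaplan-Meier estimates the probability of an event when every censored patient could still have it later. That is not true of a patient who has died. In this population the background suggests that death after distant relapse is at least as common as LR, so the competing event is not a rarity.

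Both ways of drawing the curve miss the stated endpoint:

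- **Deaths censored:** one minus Kaplan-Meier is higher than the proportion of patients with LR by 3 years. The excess grows with mortality, so it need not be equal in the two arms.
- **Deaths counted as events:** the curve is local-recurrence-free survival, a composite.

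At stake is the accuracy of one reported secondary rate, and a small distortion of its between-arm difference. Because the article names Kaplan-Meier for LR explicitly, this is a stated choice of estimator and not a detail left for a later document.

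**Working it through.** **The plan's own figure.** The article gives no expected LR rate, so there is no LR figure to reproduce. Its one computed figure is the sample size for mrTRG. The control distribution 9/39/20/32% and the simvastatin distribution 17/48/16/19% give an odds ratio for favourable grade of (0.65/0.35)/(0.48/0.52) = 2.01. The proportional-odds formula N = 12(z₁ + z₂)² / [(ln OR)²(1 − Σp̄³)], with two-sided alpha 0.05, gives N = 216 for 80% power, and 81.1% power at 222. The stated 222 with more than 80% power therefore reproduces. It does not depend on LR.

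**Size of the excess if deaths are censored.** Let *l* be the true 3-year proportion with LR and *d* the proportion who die without LR. With constant cause-specific hazards the total cumulative hazard at 3 years is −ln(1 − l − d), and LR takes the share l/(l + d). Hence

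1 − KM = 1 − exp{ ln(1 − l − d) × l/(l + d) }.

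The values of *l* and *d* are assumptions; the background's figure of under 10% local relapse guides *l*.

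| True LR | Death without LR | 1 − KM | Excess (points) | Relative |
|---|---|---|---|---|
| 5% | 10% | 5.27% | 0.27 | 5.5% |
| 8% | 10% | 8.44% | 0.44 | 5.5% |
| 8% | 15% | 8.69% | 0.69 | 8.6% |
| 10% | 10% | 10.56% | 0.56 | 5.6% |
| 10% | 15% | 10.87% | 0.87 | 8.7% |

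**Ceiling from the article's own figures.** The rationale for mrTRG and pathTRG quotes 3-year DFS of 82, 72 and 61% for favourable, intermediate and unfavourable mrTRG. Applied to the control mix in Sample size (48/20/32%), DFS events by 3 years are 0.48 × 18 + 0.20 × 28 + 0.32 × 39 = 8.64 + 5.60 + 12.48 = 26.7%. LR and death without LR are both DFS events under the usual definition, so l + d should not exceed about 26.7%, and −ln(1 − 0.267) = 0.311.

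- LR 5%, so d at most 21.7%: 1 − exp(−0.311 × 5/26.7) = 5.65%, an excess of about 0.7 points.
- LR 10%, so d at most 16.7%: 1 − exp(−0.311 × 10/26.7) = 11.0%, an excess of about 1.0 point.

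This bound is generous, because some DFS events are patients alive at 3 years with distant relapse only.

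**Comparison with sampling error.** With 111 patients per arm, the standard error of an 8% rate is √(0.08 × 0.92/111) = 2.6 points.

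**Between-arm difference.** For true LR of 8% against 6%, a difference of 2.0 points, the Kaplan-Meier difference is 2.1 points if 10% die without LR in both arms. It is 2.3 if 10% and 6% die, and 2.4 if 15% and 10% die.

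**The case against.** The strongest reply is that the article never says deaths are censored. Event and censoring rules commonly sit in the full protocol or analysis plan, neither of which is shown. That stands, and the overstatement is therefore conditional. It does not remove the point: Kaplan-Meier is fixed in print for the LR rate, and neither treatment of deaths makes it estimate the LR rate.

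The second reply is that the bias is too small to change any conclusion. That also stands. The endpoint is secondary, the excess is under one standard error, and the section on interim analyses already says that significant differences in DFS and OS need a much larger trial.

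Three stronger readings are tempting, and the article does not support them:

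- **That cancer-specific survival is wrongly estimated.** Kaplan-Meier with non-cancer deaths censored is the conventional net measure. It misleads only if its complement is read as the actual risk of cancer death. With an assumed 20% cancer deaths and 2 to 5% other deaths, that complement would be 20.2 to 20.6%. The exclusion of patients with a life expectancy under 3 years should keep other deaths few.
- **That LR and CSS cannot be derived because the data list names only PFS and OS.** That list is one summary sentence in an article. Table 1 schedules CT, CEA and lower GI endoscopy at follow-up, and the article states "Subsequent follow-up is annually". Case report fields for site of recurrence and cause of death need not appear in an article. What remains is a mismatch of labels.
- **That the relative excess could reach 16%.** This takes 10% LR with 25% dying without LR, which gives 11.58%. It implies 35% with a DFS event, above the 26.7% ceiling.

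**Conclusion.** The point holds for the 3-year LR rate, as a minor one. Kaplan-Meier is a stated estimator that does not match the stated endpoint when patients can die first. If deaths are censored the direction is certain: the LR risk is overstated. For LR of 8 to 10% with 10 to 15% competing deaths the excess is about 0.4 to 0.9 points, and it is at most about 1 point within the article's own DFS figures.

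These sizes rest on constant hazards and on assumed LR and death rates. The ceiling also assumes that the quoted DFS rates carry over to this trial's control mix. Patients with resectable metastatic disease can be admitted, and many such patients would raise it somewhat.

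The mrTRG primary analysis and the 222 patients are not affected. DFS is not affected either, since death is conventionally an event in it. The differing lists of long-term endpoints are a separate, minor inconsistency.

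**What to change.** - Estimate the 3-year LR rate in each arm by cumulative incidence (Aalen-Johansen), with death without LR as the competing event, and say so in place of the Kaplan-Meier example.
- Keep Kaplan-Meier for DFS, OS and CSS. Use cumulative incidence for cancer death, with non-cancer death competing, only if it is reported as an absolute risk.
- Use one set of long-term endpoints in the secondary objectives (now LR, DFS, CSS), Data to be collected and the Discussion (both now PFS, OS).
- Confirm that date and site of recurrence and cause of death are recorded at follow-up.

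The cost is a few sentences of analysis and endpoint wording, and a check of the case report form, with at most two fields to add if they are missing. The check is best made while follow-up is running, because site of recurrence and cause of death are harder to recover afterwards. Sample size, treatment and visits do not change.
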